### Instrumentation

We will use the Lokomat driven-gait orthosis system (Hocoma AG, Volketswil, Switzerland) integrated with a treadmill (h/p/cosmos sports & medical GmbH, Traunstein, Germany) and a motor-driven body weight support system with real time feedback control for precise body weight unloading (Lokolift, Hocoma AG) to apply RATE. A human-in-the-loop feedback system will control each subject’s active work rate by projecting his mechanical work rate onto a screen at the front of the treadmill together with a target mechanical work rate. Figure 2 illustrates the FC-RATE approach. The subject will be instructed to vary the forces applied on the exoskeleton by volitional muscle activity and to keep the actual work rate as close as possible to the target. This procedure will be used to assess the primary outcome measures (aerobic capacity), and to guide each subject’s individual target work rate during FC-RATE in the experimental group.

**Figure 2 F2:**
[figure not shown]
**Feedback-controlled robotics-assisted treadmill exercise.** The solid line represents the mechanical work rate (*P*_*mech*_) produced by the subject. The dashed line represents the target work rate (*P**_*mech*_). The passive mechanical work rate (*P*_*passive*_) is evaluated before every session and subtracted from *P*_*mech*_. Legend: *P*_*raw*_ = raw mechanical work rate, *M*_*i*_ = moments of force, *ω*_*i*_ = angular velocity, *P*_*total*_ = total mechanical work rate.

Pulmonary gas exchange and ventilatory measurements will be carried out using breath-by-breath spirometry (MetaMax 3B, Cortex Biophysik GmbH, Leipzig, Germany). Prior to each test, a volume calibration will be performed using a standardised volumetric syringe and gas calibration will be carried out using ambient air and a certified precision-analysed gas mixture. Heart rate will be continuously measured and recorded by a heart rate belt (T31, Polar Electro, Kempele, Finland) and a receiver board (HRMI, Sparkfun, Boulder, USA). Blood pressure will be monitored by a sphygmomanometer (HEM- 907, Omron Corporation, Kyoto, Japan). A software module for the overall procedure has been programmed in LabVIEW (Version 2009, National Instruments, Austin TX, USA) [33].

### Testing procedure

The first RATE session will focus on adjusting the device to provide a physiological gait pattern, and on familiarisation with the facemask for respiratory monitoring. An initial test of decreasing body weight support (BWS) continuously by 5% each minute will be carried out to define individual BWS levels. Furthermore, we will implement a short period of incremental exercise to familiarise the subject with the feedback-control structure and to estimate dynamic maximal voluntary contraction during walking (MVC-W) within the exoskeleton to adjust the individual target work rate for the following exercise tests.

We will use constant load testing (CLT) [34] to implement a constant work load during RATE. Figure 3A shows a schematic representation of the CLT protocol that consists of: (1) a rest phase where subjects will stand on the treadmill attached to the exoskeleton for 5 minutes with 0% BWS; (2) a passive phase where subjects will walk passively with their individual BWS for 5 minutes; and (3) an active phase where subjects will be instructed to actively contribute to the walking by pushing forward within the exoskeleton during the swing phase of each leg to reach the target work rate, which will be defined as 40% of MVC-W. The target work rate profile will be displayed on a screen in front of the subject. Using real-time visual feedback of their actual work rate the subjects will be asked to maintain their active contribution as close as possible to the target work rate. This phase will be terminated after 10 minutes; (4) passive phase/recovery: subjects will be instructed to walk passively with their individual BWS for 5 minutes; (5) rest: subjects will stand on the treadmill, still attached to the exoskeleton, for 5 minutes with 0% BWS.

**Figure 3 F3:**
[figure not shown]
**Exercise testing protocols.** Schematic representation of constant load testing **(A)** and incremental exercise testing **(B)** using feedback-controlled robotics-assisted treadmill exercise. The solid line represents the mechanical work rate (*P*_*mech*_) produced by the subject. The dashed line represents the target work rate (*P**_*mech*_). The slope will be estimated such that the predefined peak work rate is reached after 10 minutes. When individual termination criteria are met the incremental phase is ended and *P**_*mech*_ set back to the passive level.

Incremental exercise testing (IET) [35] will be used to estimate peak cardiopulmonary performance parameters. Figure 3B shows a schematic representation of the IET protocol that consists of: (1) a passive phase where subjects will be instructed to walk passively with their individual BWS for 5 minutes; (2) and active phase where subjects will be instructed to actively contribute to the walking by pushing forward within the exoskeleton during the swing phase of each leg to reach peak exercise capacity, where the slope will be defined so that MVC-W is reached in approximately 10 minutes; and (3) a passive phase/recovery where subjects will be instructed to walk passively with their individual BWS for 5 minutes.

Both test protocols will follow strict termination criteria for cardiopulmonary exercise testing including: (1) abnormal blood pressure responses, that is, hypertensive (systolic BP >210 mmHg or diastolic BP >115 mmHg) when exercising at high work rate, or hypotensive responses (decrease in BP >10 mmHg) despite an increase in work rate; (2) individual work rate below target work rate for 60 s; (3) peak heart rate within 10 beats per minute of the age-predicted heart rate maximum [36], where the formula will be adjusted down to 70% of heart rate maximum for subjects on β-blocker medications [37]; and (4) pain or discomfort in the chest. We will follow established models for cardiopulmonary exercise testing based on the ACSM guidelines [24].

The 10MWT and the 6MWT will be conducted using standardised testing protocols in a quiet area. Standing function will be assessed within parallel bars. The SIS will be administered to the subjects on a face-to-face basis.

### Intervention

Both groups will receive regular RATE sessions (3/week, 30min/session) during their inpatient rehabilitation period (typically, 4 to 12 weeks). Training intensity will be recorded by continuous heart rate monitoring and evaluating rate of perceived exertion (RPE) on the 6 to 20 scale [38]. The experimental group will receive progressive cardiovascular exercise using FC-RATE. Training will start at 40% of peak work rate (based on initial IET results) for the first session. Intensity will then be adjusted by increasing the target work rate in 5% steps for subsequent sessions based on heart rate and RPE outcomes (target heart rate: 40 to 70% of heart rate reserve, target RPE: 11 to 14). The control group will receive conventional RATE, where therapists will focus on gait quality only. To confirm or refute low cardiovascular training intensity in the control group (target heart rate: ≤30% of heart rate reserve, target RPE: ≤7), therapists will monitor heart rate and RPE during all training sessions. All subjects will receive individually tailored conventional therapy including physiotherapy (4 to 5 sessions/week, 30 to 60min/session), occupational therapy (2 to 3 sessions/week, 30 to 60min/session), and individual speech and language therapy.

### Safety arrangements

There is an inherent risk during cardiopulmonary exercise testing procedures and cardiovascular intervention programmes for subjects with sub-acute stroke of a recurrent cerebral or cardiac event. Furthermore, subjects are attached to the exoskeleton, which complicates emergency procedures. Several risk management arrangements will be implemented to ensure subjects’ safety: (1) clearly defined eligibility criteria to include medically stable subjects only, (2) continuous blood pressure monitoring during exercise testing (noted above), (3) presence of resuscitation-trained assistants, (4) opportunity to call the medical resuscitation team in the clinic, and (5) presence of personnel trained to release the subject within 60 s from the exoskeleton.

### Sample size and power calculation

The required sample size has been calculated based on pooled estimation of standardised effect sizes obtained from a previous meta-analysis on cardiovascular exercise early after stroke [18]. Power analysis was done using G*Power Software (Version 3.1, University of Dusseldorf, Germany). *A priori* analysis indicated that a sample of at least 14 subjects would provide a statistical power of 80%, that is, an 80% (β = 0.2) chance to detect a 20% (α = 0.05) difference between groups. To allow for dropouts, a total of 20 subjects will be recruited.

### Data management and analysis

Data will be recorded on standardised forms and concealed between examiners and therapists. All data recorded continuously during testing will be saved automatically by the software module and will only be accessible by an independent software specialist. Data set examples will be checked for errors randomly or at any time a serious adverse event occurs. Raw breath-by-breath data will be processed using a zero phase shift moving average filter over 15 breaths [39]. Peak cardiopulmonary response variables will be calculated by analysing the final 30 s during incremental exercise, whereby criteria for maximal aerobic capacity will be (1) plateau in oxygen uptake, (2) respiratory exchange ratio (RER) ≥1.15, and (3) peak heart rate within 10 beats per minute of the age-predicted heart rate maximum (adjusted for subjects on β-blocker medications) [24]. Further peak performance variables will be defined as the maximal values at the termination time of the IET. The gas exchange threshold (GET) will be estimated using the v-slope method and standard gas exchange criteria [40]. Step response kinetics will be calculated using a non-linear least-squares algorithm to fit the data as described in the following mono-exponential equation: VO_2(t)_=VO_2_(b)+ΔVO_2_(1-e^-(t-Td)/τ^), t > 0, with VO_2_(b) = oxygen uptake at baseline, ΔVO_2_ = step increase in oxygen uptake, Td = time delay of 20 s corresponding to the cardiodynamic phase of the response, and τ = time constant [34]. Steady-state will be defined as the mean value of the final 120 s during constant load phases. All analyses will be performed using MATLAB (Version R2010a, MathWorks, Natick MA, USA) and MetaSoft (Version 3.9.6 SR1, Cortex Biophysik GmbH, Leipzig, Germany).

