**Primary outcomes (Aerobic capacity)**		
Peak oxygen uptake (VO_2_peak)	Peak oxygen uptake in the last 30 s during IET	mL/min, mL/min/kg
Peak work rate (Ppeak)	Maximal work rate during IET	W
Peak heart rate (HRpeak)	Maximal heart rate during IET	beats/min
Peak ventilation rate (V_E_peak)	Peak ventilation rate in the last 30 s during IET	L/min
Peak respiratory rate (R_f_peak)	Peak respiratory rate in the last 30 s during IET	1/min
Peak respiratory exchange ratio (RERpeak)	Value of the oxygen uptake and carbon dioxide output relationship at peak oxygen uptake	dimensionless
Gas exchange threshold (GET)	Oxygen uptake at the point at which carbon dioxide output begins to increase more rapidly in proportion to oxygen uptake during IET. Estimated using the v-slope method and standard gas exchange criteria	mL/min, mL/min/kg
Oxygen cost of work (ΔVO_2_/ΔP)	Δ oxygen uptake/Δ work rate	mL/min/W
Heart rate response (ΔHR/ΔVO_2_)	Δ heat rate/Δ oxygen uptake	beats/mL/min
Peak oxygen pulse (VO_2_peak/HRpeak)	Peak oxygen uptake/peak heart rate	mL/beat
Time constants of oxygen uptake during on-/off-transition (τ)	Time taken for oxygen uptake to reach 63% of its increment magnitude, when the response is modelled as a mono-exponential function during CLT	s
Steady-state increase in oxygen uptake (ΔVO_2_)	Steady-state increase in oxygen uptake following a step increase/decrease in exercise intensity during CLT	mL/min, mL/min/kg
Steady-state increase in heart rate (ΔHR)	Steady-state increase in heart rate following a step increase/decrease in exercise intensity during CLT	beats/min
Steady-state increase in ventilation rate (ΔV_E_)	Steady-state increase in minute rate following a step increase/decrease in exercise intensity during CLT	L/min
Steady-state increase in respiratory rate (ΔR_f_)	Steady-state increase in respiratory rate following a step increase/decrease in exercise intensity during CLT	1/min
Oxygen cost of work during constant load (VO_2_/P)	Oxygen uptake versus work rate during passive and active constant load phases	mL/min/W

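### The on-transition oxygen time constant τ, listed as primary, is fitted as a response to an instantaneous step, so the time a subject takes to reach the target work rate lengthens it, and only one arm practises that task

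*Protocol article*

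**What the plan says.** Table 1 places τ, for the on- and off-transitions of constant load testing, under the primary outcomes and defines it as "Time taken for oxygen uptake to reach 63% of its increment magnitude, when the response is modelled as a mono-exponential function during CLT".

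The Data management and analysis section gives the method: "Step response kinetics will be calculated using a non-linear least-squares algorithm to fit the data as described in the following mono-exponential equation". The equation is VO2(b) + ΔVO2(1 − e^−(t−Td)/τ), with "Td = time delay of 20 s corresponding to the cardiodynamic phase of the response". Measured work rate is not an input.

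The Instrumentation section says that the subject generates the work rate through voluntary muscle activity, with actual and target values shown on a screen. For the 10-minute active phase the target is 40% of the maximal voluntary contraction during walking, and "the subjects will be asked to maintain their active contribution as close as possible to the target work rate". Both test protocols stop if work rate stays below target for 60 s (Testing procedure). Tracking error, as a root mean square, is a separate secondary outcome.

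Under Intervention, the experimental arm trains with the feedback-controlled task. The control arm trains for gait quality only.

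**The concern.** The stated equation is the response of a first-order system to a load that jumps to its final value at t = 0. Here only the target jumps. The load follows as fast as a severely impaired subject can produce it, and the equation attributes that delay to oxygen kinetics.

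If the delay were the same at every visit and in both arms, it would inflate τ and add between-subject noise but would not bias the comparison. The design gives a reason why it may not stay the same: the experimental arm practises target tracking three times a week on the task used in the test, and the control arm does not. A faster rise to target after training would shorten on-transition τ in one arm with no change in physiology, and a primary measure would then suggest a benefit.

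Two features of the plan do not remove this. The fixed 20 s delay is assigned to the cardiodynamic phase, not to tracking lag. The tracking-error outcome has no sign, is not specific to the transition, and is not linked to the τ fit.

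**Working it through.** **Inputs from the article:** the mono-exponential equation, Td = 20 s, a 10-minute active phase, and the 60 s below-target rule.

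**Assumed, because the article gives no figures:** true τ of 45 s (range 30 to 60 s); work rate reaching target either exponentially, P(t) = 1 − e^(−t/τP), or by a straight ramp of length T; fitting from t = 20 s. The article does not say whether VO2(b) is fixed beforehand or estimated in the fit, so both are shown.

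**1. The plan's own figure.** After one time constant, 1 − e^(−1) = 0.632, the 63% in Table 1. A noise-free true step, fitted with the stated equation, returns 45.1 s (baseline fixed) and 45.0 s (baseline free) for a true 45 s. The method is sound when the input is a step.

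**2. Expected effect.** For a first-order response, the area between the final level and the response, divided by the step size and net of Td, is τ + τP for an exponential rise and τ + T/2 for a ramp. A 10 s rise constant gives 45 + 10 = 55 s; a 30 s ramp gives 45 + 15 = 60 s. The fits below should lie near these values when the baseline is fixed.

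**3. Fitted τ for a true 45 s (noise-free, unfiltered).**

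| Work-rate rise | Baseline fixed | Baseline free |
|---|---|---|
| Rise constant 5 s | 50.8 s (+5.8) | 47.2 s (+2.2) |
| Rise constant 10 s | 56.8 s (+11.8) | 51.0 s (+6.0) |
| Ramp over 15 s | 53.6 s (+8.6) | 48.3 s (+3.3) |
| Ramp over 30 s | 62.7 s (+17.7) | 53.9 s (+8.9) |

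For true τ of 30 and 60 s, a 10 s rise constant gives 41.4 and 72.3 s (fixed) or 36.9 and 65.4 s (free).

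With the planned 15-breath filter (assumed 24 breaths/min), a true step reads 46.1 s (fixed) and 46.9 s (free). Against that reference a 10 s rise constant adds 57.4 − 46.1 = 11.3 s (fixed) or 52.2 − 46.9 = 5.3 s (free), and a 30 s ramp adds 63.1 − 46.1 = 17.0 s or 54.4 − 46.9 = 7.5 s. The filter does not change the picture.

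**4. What tracking practice could do.** If the rise constant falls from 10 to 5 s, τ drops by 56.8 − 50.8 = 6.0 s (fixed) or 51.0 − 47.2 = 3.8 s (free). If a ramp shortens from 30 to 15 s, the drop is 62.7 − 53.6 = 9.1 s or 53.9 − 48.3 = 5.6 s. True τ is 45 s throughout.

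**5. What the 60 s rule excludes.** The exponential shortfall at 60 s is e^(−60/τP): 13.5% for τP = 30 s, 5.0% for 20 s, 0.25% for 10 s, and negligible for 5 s. Taken literally an exponential never reaches target, but 0.25% is immaterial; 5% and 13.5% are not, and such tests would be expected to stop. A 30 s ramp reaches target at 30 s and is allowed. A continuous fade would also trigger the rule.

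**6. Using the measured work rate as input.** With the work-rate trace driving the same first-order model, noise-free fits return 30.0, 45.0 and 60.0 s in every pattern tested. This shows that the algebra works, but the data came from the same model, so it does not show that the model fits patients.

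**The case against.** - **Poor tracking is not shown.** The target is submaximal, subjects have real-time feedback, and a familiarisation session comes first. Listing tracking error as an outcome shows that tracking is monitored, not that it is bad. This stands: the size is conditional on assumed rise times.
- **Large distortions are bounded.** A reader might infer errors of 20 to 40 s from slow rises, or a marked shortening of τ from fading effort. The 60 s rule limits both, and slow onset and fading act in opposite directions. The article does not support these larger figures.
- **The size depends on the fit.** A reader might take fitted τ to be simply physiological τ plus rise time. That is roughly so only with a fixed baseline; a free baseline about halves the effect or better.
- **τ is defined by this model, with a cited method.** True, and the article does not contradict itself here. But the method is stated, not left to a fuller document, and it assumes an input that the device does not impose.
- **Scope is narrow.** τ is one of 16 rows listed as primary. The off-transition only requires the subject to stop pushing, so it should be closer to a step. Error common to both arms is not bias between them.
- **The alternative fit has its own errors.** For a true 45 s and a 10 s rise, misaligning the traces by 5 s either way gives 39.7 or 49.4 s. If measured work fades by 10% while the metabolic input does not, it gives 51.4 s. This argues for reporting it beside the stated fit, not in place of it.

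The unequal tracking practice between arms is left unanswered by these points.

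**Conclusion.** The point holds for the on-transition τ. Fitted as stated, it mixes oxygen kinetics with the time the subject takes to reach the target. For an assumed true τ of 45 s, the lengthening is about 2 to 6 s (baseline free) to 6 to 12 s (baseline fixed) for rise constants of 5 to 10 s, and about 8 to 18 s for a 30 s ramp. Because only the experimental arm trains with the feedback task, a faster rise after training could pass for improved kinetics.

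A reader might infer that the comparison of τ is already known to be biased, or that the primary outcomes as a whole are compromised. The article supports neither: it reports no rise times by arm, and VO2peak does not come from this fit. What it does establish is that, as planned, a group difference in on-transition τ could not be told apart from a difference in tracking.

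**What to change.** For the on-transition, add a second fit in which VO2 is a first-order response to that test's recorded work rate: τ·dVO2/dt = G·P(t − Td) − (VO2 − VO2(b)), with gain G, time constant τ and the same 20 s delay. P is work rate above the passive level. Then:

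- report this τ beside the ideal-step τ;
- state whether VO2(b) is fixed or estimated, and use the same choice in both fits;
- report the work-rate rise time by arm and visit;
- do not attribute a group difference in τ to oxygen kinetics unless the measured-input fit agrees.

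The cost is a small change to the MATLAB code. No new measurement should be needed, since "All data recorded continuously during testing will be saved automatically by the software module" and tracking error is already computed from actual work rate. There are two conditions. The work-rate and gas-exchange traces must be time-aligned, which the article does not document for the separate devices. The fit also assumes a constant gain between measured work rate and VO2. Both should be checked before the second fit is relied on.

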### Statistical analysis

Descriptive statistics will be calculated for dependent and independent variables. Demographic and clinical characteristics of the groups will be compared on admission using unpaired two-sample *t*-tests (continuous data) and Chi-square analysis (categorical data). Nonparametric methods will be used when assumptions of normality are violated. To evaluate the clinical efficacy of the method, group differences will be compared after each 4-week intervention (t1, t2, t3, *etcetera*) using unpaired two-sample *t*-tests for continuous data and z-tests for categorical data that conform to the assumption of normality. If data are not normally distributed for continuous variables, Mann-Whitney *U* tests will be applied. A mixed effects analysis of variance with repeated measures to model the intervention effects over time for continuous variables that are normally distributed (that is, aerobic capacity) will be applied. Non-parametric tests (Mann-Whitney *U* and Kruskall Wallis tests) will be used for categorical data (that is, SIS) or where a normal distribution is not present. Variables that are significantly different in the baseline analysis will be used as covariates for further analysis. Multiple regressions will be applied to evaluate relationships among variables. All statistical analysis will be performed using SPSS (SPSS Inc., Chicago, Il, USA). The significance level will be 0.05.

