### Outcome measures

All primary and secondary outcome measurements will be carried out at baseline (t0), after each 4-week intervention period (t1, t2, t3, *etcetera*), and before clinical discharge. At baseline, descriptive variables for each subject include age, sex, area and type of infarct, side of stroke, time since stroke onset, body height and body mass.

A summary of the primary and secondary outcome measures can be found in Table 1. The primary outcome will be aerobic capacity, the accepted criterion for exercise capacity [24]. We will estimate standardised cardiopulmonary performance parameters based on international guidelines [25]. Secondary outcome measures will focus on physical performance, stroke impact, and feasibility. We will evaluate the work rate tracking error during FC-RATE by calculating the root mean square error (RMSE) between actual work rate and target work rate values. Gait speed will be assessed using the 10 Meter Walk Test (10MWT) [26,27]. Walking endurance will be measured using the 6 Minute Walk Test (6MWT), the distance that an individual is able to walk in 6 minutes on a hard, flat surface [28,29]. To assess basic standing function in non-ambulatory subjects, we will employ a standardised standing test on a force plate. The subject will be requested to: (1) stand in bipedal stance, (2) shift his/her body weight from the right to the left leg alternately, and (3) shift his/her body weight in a defined rhythm from the right to the left leg alternately. The test-retest reliability of centre of pressure measures in bipedal tasks has been shown previously [30]. We will use the Stroke Impact Scale (SIS) to assess recovery and quality-of-life after stroke [31].

**Table 1 T1:** Overview of primary and secondary outcomes

**Variable**	**Details**	**Unit**

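### Covariates are chosen by baseline significance tests, and the tests named for efficacy carry no baseline term although every outcome is measured at t0

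*Protocol article*

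**What the plan says.** Three statements matter, two in Statistical analysis and one in Outcome measures.

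- **Covariates.** Group characteristics on admission are compared by t-tests or Chi-square tests, and "Variables that are significantly different in the baseline analysis will be used as covariates for further analysis". No covariate is fixed in advance. The article does not say whether baseline VO2peak is among the characteristics tested.
- **Efficacy.** "To evaluate the clinical efficacy of the method, group differences will be compared after each 4-week intervention", by unpaired t-tests, or Mann-Whitney tests if the data are not normal. Neither a baseline term nor a change score is mentioned.
- **Available data.** "All primary and secondary outcome measurements will be carried out at baseline (t0), after each 4-week intervention period", so each subject has a baseline value of each outcome.

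The same section also plans a second analysis: "A mixed effects analysis of variance with repeated measures to model the intervention effects over time for continuous variables that are normally distributed", with aerobic capacity as the example. It does not say whether t0 is a level of the time factor, or whether this model or the per-visit tests decide efficacy. SIS and non-normal outcomes are sent to rank tests. On alpha the article says "The significance level will be 0.05", without sidedness.

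**The concern.** Under randomisation any baseline difference between arms is due to chance. Its p-value therefore says nothing about whether the variable predicts the outcome, which is the reason to adjust for it. In a trial this small the test is also insensitive, so sizeable chance imbalances pass as non-significant and go straight into the post-treatment comparison. The analysis model then depends on a pre-test that has no bearing on its merit.

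The per-visit t-tests also leave all between-subject spread in the error term. If VO2peak at baseline predicts VO2peak at follow-up, that costs power. The article's Conclusion makes further full-scale trials depend partly on potential for efficacy on aerobic capacity, so the precision of this comparison matters.

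**Working it through.** **Inputs from the article:** at least 14 subjects for 80% power and 20 recruited (Sample size and power calculation); alpha 0.05.

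**Assumptions:** 1:1 allocation, so 7 to 10 per arm; two-sided tests; normal outcomes with SD 1; baseline VO2peak is among the variables tested; baseline-to-follow-up correlation r from 0.3 to 0.8, because the article gives none.

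**1. The article's own figure.** The 14 subjects cannot be reproduced, because neither a standardised effect nor an SD is printed. Solved backwards, 7 per arm with a two-sided t-test needs d = 1.63 for 80% power. The calculations below therefore use a separate illustrative effect of 0.8 SD.

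**2. Smallest observed difference that is flagged:** t(0.975, 2n−2) × √(2/n).
- n = 10: 2.101 × 0.447 = 0.94 SD.
- n = 7: 2.179 × 0.535 = 1.16 SD.

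**3. How often a large imbalance goes unflagged.** The baseline difference has SD √(2/n).
- n = 10: P(|D| > 0.5) = 2[1 − Φ(0.5/0.447)] = 26.4%. Subtracting the 5% that are flagged leaves about 21%.
- n = 7: 2[1 − Φ(0.5/0.535)] = 35.0%. Subtracting 5% leaves about 30%.

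Simulation (40,000 trials per setting) gives the same figures.

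**4. Consequence in those trials.** The post-value difference is shifted by r × D. The mean |D| in these trials is about 0.66 SD (n = 10) or 0.73 SD (n = 7). At r = 0.7 the shift is 0.7 × 0.66 = 0.46 SD or 0.7 × 0.73 = 0.51 SD. The simulated conditional type I error of the post-value t-test for r = 0.3 to 0.8 is about 6-10%. With ANCOVA the shift is about 0 and the error about 5%.

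**5. Overall type I error of the rule:** about 5% at r = 0.3, 4.5% at 0.5, 3.6% at 0.7 and 3.2% at 0.8 (n = 10). It is not inflated.

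**6. Power.** Relative to the post-value t-test, the large-sample standard error of the treatment difference is √(1−r²) for ANCOVA and √(2(1−r)) for a change score. A change score is what the group-by-time test amounts to with t0 and one follow-up. Simulated power for 0.8 SD, n = 10 (runs differ by about one point):

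| r | SE ratio, ANCOVA | SE ratio, change | Plan's rule | Group-by-time with t0 | ANCOVA |
|---|---|---|---|---|---|
| 0.3 | 0.95 | 1.18 | 40% | 30% | 41% |
| 0.5 | 0.87 | 1.00 | 39% | 39% | 48% |
| 0.6 | 0.80 | 0.89 | 40% | 48% | 54% |
| 0.7 | 0.71 | 0.77 | 40% | 59% | 63% |
| 0.8 | 0.60 | 0.63 | 40% | 76% | 78% |

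With n = 7, rule versus ANCOVA is 28% v 38% at r = 0.6 and 28% v 59% at r = 0.8. If baseline VO2peak is not among the tested variables, the rule reduces to the post-value t-test, whose power is about 39-40% at n = 10.

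**The case against.** The strongest reply is that the article does plan a baseline-using analysis. The repeated-measures ANOVA names aerobic capacity and is described as modelling intervention effects. If t0 is a time level, its group-by-time term uses baseline in every trial, whatever the pre-test shows. A reader might therefore infer from the t-tests that baseline is wholly wasted; the article does not support that. At r of 0.7 or more this model loses only 2 to 4 points to ANCOVA.

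The reply has limits. At r of 0.5 or below the model recovers nothing, and at 0.3 it does worse than the post-value test. It also over-corrects imbalance, by about 0.20 SD at r = 0.7 in the trials described in step 4. The article does not name it as the efficacy test or say that t0 is in it. It does not cover SIS or non-normal outcomes, and the rank tests named for those cannot carry a covariate.

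Three further objections are right:
- A reader might infer a false-positive problem. Overall type I error is at or below 5%; only the error in imbalanced trials is raised.
- A reader might infer that power is roughly halved. That fits only r near 0.8. At 0.6 the loss is about a quarter ((54 − 40)/54 = 26%), and at 0.3 almost nothing.
- The trial is an exploratory pilot and the randomised comparison is unbiased on average, which argues against the highest severity.

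It could also be said that an article leaves analysis detail to a fuller document. That covers the choice of primary model, but not the covariate rule, which the article states outright.

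**Conclusion.** The point holds as a should-fix. The covariate rule is stated and unsound, and the tests named for efficacy omit a baseline value that the trial collects. Imbalances of up to about 0.94 SD (10 per arm) or 1.16 SD (7 per arm) go unadjusted. The harm is conditional bias and lost power, not inflated overall type I error.

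The imbalance figures rest on 1:1 allocation, normality and two-sided testing. The size of the power loss also rests on a correlation that the documents do not give: about 1 point at r = 0.3, 9 at 0.5, 14 at 0.6, 23 at 0.7 and 38 at 0.8, for a 0.8 SD effect with 10 per arm. If the planned ANOVA includes t0 and is read as the efficacy test, the loss for aerobic capacity shrinks to 2 to 4 points at r of 0.7 or more.

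**What to change.** Delete the sentence that makes covariates depend on baseline significance. State instead that the between-group efficacy comparison of VO2peak and the other continuous outcomes is adjusted for the baseline value of the same outcome, by ANCOVA or a baseline-adjusted mixed model, whatever the baseline comparison shows. Keep the baseline table descriptive.

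This changes wording in the Statistical analysis section only and uses data already collected. It costs one residual degree of freedom; even at r = 0.3 the simulated power is no lower than under the rule (41% v 40%, n = 10). Making t1 the sole time point, or adding time since stroke as a further covariate, is optional and not part of this fix.
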